#### 2.10.6. Covariates

The covariates we will consider, at a minimum, are: (a) two terms implementing a quadratic trend for number of months since the start of the program, (b) a student's preferred substance (i.e., alcohol, cannabis, or nicotine), (c) a student's baseline level of dependence for his or her primary substance (based on appropriate self-report questionnaires), (d) number of repeat substance use infractions that a student has, (e) number of peers who use drugs, (f) a student's age at baseline, (g) a student's gender (or if cell counts are too low, biological sex), and (h) whether school is urban, rural, or suburban. These covariates will be used as part of missing data imputation, and if necessary, may be included in the primary analysis (to be determined during the analyst-blind period). If any additional covariates will be deemed necessary for inclusion, this will be done before the blind is broken for the analyst.

#### 2.10.7. Missing data

Analysis of the primary outcome will require students to provide a pair of observations and the number of days spent using a substance at both time-of-infraction and post-discipline time points. If there is loss to follow-up, there then is the risk that a pairwise deletion of data points will (a) lead to a substantial reduction in sample size, and (b) risk bias in estimates if loss to follow-up is systematically different between those undergoing standard disciplinary actions vs. those enrolled in the iDECIDE program. Missing data will therefore be handled via multivariate imputation by chained equations (47). Values for missing observations will be imputed 40 times using baseline sample characteristics: (a) a student's preferred substance (i.e., alcohol, cannabis, or nicotine), (b) a student's baseline level of dependence for his or her primary substance (based on appropriate self-report questionnaires), (c) number of repeat substance use infractions that a student has, (d) number of peers who use drugs, (e) student's age at baseline, (f) a student's gender (or if cell counts are too low, biological sex), and (g) whether school is urban, rural, or suburban. The analyses will be rerun for each set of imputations and results will be pooled by combining the posterior draws across imputations to obtain appropriate estimates and measures of uncertainty.

#### 2.10.8. Inverse probability weights

The longitudinal aspect of the study design, combined with an inherent possibility of treatment contamination, results in a risk that sample characteristics may differ between the start of the study and the end of the study. For example, in the initial months of the program, the sample will consist of a mix of students more and less responsive to the intervention. However, in later months, students who would be more responsive to the intervention but have not yet committed an infraction could be influenced by students who already received the intervention, and thereby become less likely to commit infractions in the first place. In this scenario, sample characteristics will thereby shift in later months to consist more of less responsive students, resulting in biased estimates that do not properly reflect the efficacy of the study.

We can correct for potential bias due to differing sample characteristics via inverse probability weights (48). Note, however, that standard methods for inverse probability weights (IPW) do not translate easily to Bayesian settings. Therefore, we will either fully implement the two-step method proposed by Liao and Zigler (49), or if computational challenges make this infeasible, implement a pseudo-Bayesian approach. The first step will be to compute the IPW by re-administering a custom school-wide survey (used as part of screening) to students who are enrolled in the study. We will fit a logistic regression predicting referral status (pre- vs. post-intervention) for each student using the following predictors from the survey: (1) whether a student is an athlete (yes or no), (2) a student's grade-point average, (3) a student's post-graduation plans (four-year college, two-year college, trade school, military, getting a job, unknown, and an “other” category), (4) prior suspensions (none, drug-related, and other), (5) race, and (6) ethnicity.

We will then compute stabilized weights per subject (i.e., the unconditional probability of referral divided by the probability of referral conditioned on the predictors from the school-wide survey) per each posterior draw. The second step will be to use the stabilized weights to adjust the likelihood for the statistical model used with the primary analysis. This can either be done (1) in a fully Bayesian fashion, using the full set of stabilized weights computed per each posterior draw from step one, or, if this proves computationally infeasible, (2) in a pseudo-Bayesian fashion, using the weight per subject averaged over posterior draws (i.e., maximum a posteriori estimates for weights). The likelihood used for sampling from the posterior will be re-weighted by the subject-level weights to adjust for potential confounding due to differing sample composition.

#### 2.10.9. Model specifics for secondary outcomes

Change in quality of relationships with teachers/administrators, school connectedness, social and emotional satisfaction at school (36) will be evaluated as secondary outcomes. Summed scores from the emotional support form will be assumed to follow a binomial distribution, analyzed with an equivalent statistical model, and used for the number of days spent using a preferred substance.

#### 2.10.10. Sensitivity analyses

For all outcomes, we will conduct at least five sensitivity analyses. We will examine how robust our conclusions are to implementation of the intent-to-treat approach and also conduct an as-treated analysis, restricting comparisons for the key effect to students confirmed to have received standard disciplinary action pre-intervention vs. students confirmed to have attended iDECIDE sessions post-intervention. We will examine how robust our conclusions are to the assumption of additivity with the quadratic time trend and will fit an interaction model to examine (a) the statistical significance of the interaction terms between the key comparison and the quadratic time trend, and (b) the difference in performance on the leave-one-out cross-validation (LOO-CV) approximation between the additive and interaction models. We will examine how robust our conclusions are to the assumption of additivity with the three types of substances (alcohol, nicotine, and cannabis) and will again fit an interaction model and examine (a) the statistical significance of the interaction terms between the key comparison and the categorical predictors for substance type, and (b) the difference in performance on the LOO-CV approximation between the additive and interaction models. We will examine how robust our conclusions are to our missing data approach, rerunning the primary analysis using only observed data. Finally, we will examine how robust our conclusions are to implementation of the IPW approach, rerunning the primary analysis without inclusion of the stabilized weights.

#### 2.10.11. Enrollment of additional schools

It is possible that additional schools will enroll in the iDECIDE program post-randomization (for example, a school may choose to enroll in the second year of the study). Schools that enroll after the initial randomization will be excluded from primary analyses, as randomization for schools that enroll later will result in especially skewed distributions across waves (there will be fewer waves for schools that enroll later to be randomized across). However, assuming sufficient schools enroll post-randomization, we will conduct a secondary analysis to examine whether conclusions change when including schools that enroll late in the program.

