## 2. Materials and methods

### 2.1. Design

We will conduct a Type 1, hybrid effectiveness-implementation trial (23) guided by Proctor's implementation model (24). Using a stepped wedge design with approximately 90 schools, we will randomly allocate the timing of implementation of the iDECIDE curriculum compared to standard disciplinary response, over approximately 36 months. Timing of curriculum implementation will be staggered over seven clusters, with each cluster composed of ~7–15 schools (size of clusters accounting for districts randomized together). One cluster of schools will cross from control (unexposed phase) to intervention (exposed phase) approximately every two to three school months until all schools are exposed to iDECIDE. This design will allow transition periods for training of school-based facilitators, during which clusters will not be considered as either in the control (unexposed) or intervention (exposed) phase of the study. See Figure 1 for the approximate stepped wedge schema.

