### 2.2. Partnering schools

Middle and high schools across all 351 municipalities in Massachusetts were given the opportunity to participate in this trial. Proactive school recruitment occurred across a period of approximately 12 months. Schools had the opportunity to attend an informational session about iDECIDE and/or meet one-on-one with members of the evaluation team to discuss study involvement. Recruitment for schools occurred through state listservs, word of mouth, and facilitated introductions through DPH, local community coalitions, and other community agencies. Inclusion criteria for schools include (1) middle or high school, serving grades 6-12, (2) agreement to refer students with a school-based substance use infraction to the MGH evaluation team (unless opted out by the student's parent/legal guardian; see section on Consent or Assent below), and (3) a signed letter of commitment from the appropriate school/district representative.

The first school cohort was enrolled in January 2022 (Cohort 1; *n*_schools_ = 69 schools). Due to substantial unsolicited interest in the curriculum from schools following the return to in-person learning after the COVID-19 pandemic, one additional wave of schools was onboarded and separately randomized in September 2022 (Cohort 2; *n*_schools_ = 33 schools).

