#### 2.10.12. Power

We determined power using the R package “swCRTdesign” (50) which was explicitly designed to estimate power for stepped wedge designs. We were able to power the study using student enrollment data and publicly available data on 2018–2019 drug infraction rates (51) for the 67 schools who agreed to participate as part of Cohort 1. There were 16 schools without infraction rate data. For simplicity, this missing data was imputed by examining 522 schools with complete data, identifying schools that matched in type (e.g., middle school, high school, etc.) and had the closest number of students. Infraction rates from this subset of schools of the same type and equivalent student size were then substituted for the missing values.

The number of participants per cluster will not depend on the schools assigned to the cluster, but rather the number of students in the schools who will have a substance use infraction. We cannot know the exact number in advance, but we can simulate the predicted number of participants via a binomial distribution using student enrollment for the upcoming 2 years and the infraction percentages from 2018 to 2019. Following the proposed stratified randomization scheme we will use in the actual study, schools were assigned to each cluster at the district-level, stratified by whether a district had any middle schools (yes/no) and school size (using a median split of 1,460 for districts with middle schools and 829 for those without). This approach for generating sample sizes was repeated 100 times to integrate over uncertainty and the final estimate of power was obtained by averaging over the repetitions. As noted earlier, to determine the number of waves to use, we examined power assuming four waves, seven waves, and 10 waves.

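### Read literally, the late-enrolment exclusion removes the 33 randomised Cohort 2 schools from the primary analysis and conflicts with the design of about 90 schools

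*Protocol article*

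**What the plan says.** Four places in the protocol article bear on which schools form the primary analysis set.

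- Section 2.1 (Design) sets the scale: "Using a stepped wedge design with approximately 90 schools". It adds: "Timing of curriculum implementation will be staggered over seven clusters, with each cluster composed of ~7–15 schools". The abstract also gives about 90 schools.
- Section 2.2 (Partnering schools) reports enrolment as done: "The first school cohort was enrolled in January 2022 (Cohort 1; *n*_schools_ = 69 schools"), followed by "one additional wave of schools was onboarded and separately randomized in September 2022 (Cohort 2; *n*_schools_ = 33 schools"). Section 2.5 confirms that the two cohorts were randomised separately.
- Section 2.10.11 (Enrollment of additional schools) gives the exclusion: "Schools that enroll after the initial randomization will be excluded from primary analyses". The reason is that later schools have fewer waves left to be spread over, so their distribution across waves would be skewed. Such schools go to a secondary analysis if enough of them enrol. The section treats late enrolment as a possibility and gives a school joining in the second year as its example.
- Section 2.10.12 (Power) uses data "for the 67 schools who agreed to participate as part of Cohort 1" and reports power of 0.82 for seven waves.

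No section says whether Cohort 2 is in or out of the primary analysis.

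**The concern.** Cohort 2 was onboarded and randomised about eight months after Cohort 1 was enrolled. In plain words it enrolled after the initial randomisation, so the exclusion covers it. The design section nevertheless describes a trial of a size that only the two cohorts together can reach. The article therefore describes one trial in Section 2.1 and a smaller one in Section 2.10.11.

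At stake are the definition of the primary analysis set and about a third of the randomised schools. These schools will already have been randomised and will be referring students, so leaving them out of the primary analysis saves no effort in the field. It also sits awkwardly with the intent-to-treat commitment in Section 2.10.4.

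**Working it through.** **School counts.** Inputs: 69 and 33 (Section 2.2), about 90 (Section 2.1), 67 (Section 2.10.12).

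- Both cohorts: 69 + 33 = 102.
- Share removed by the literal rule: 33/102 = 32%.
- Remaining schools against the design figure: 69/90 = 77%, which is 21 short.
- Average per wave over seven waves: 69/7 = 9.9; 102/7 = 14.6. Both fall within the stated range of about 7–15 per cluster, so that range does not settle which count was meant.

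Neither 69 nor 102 is about 90, but about 90 cannot be reached without Cohort 2.

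**The plan's own power figure.** The number of students per school is not given, so 0.82 cannot be reproduced independently. A consistency check is possible with a stepped-wedge linear mixed model: fixed period effects, schools of equal size as clusters, difference 0.2, SD 0.79, ICC 0.02, CAC 0.22 and 67 schools. The article does not state the alpha used for power, so both 0.05 and 0.025 (two-sided) were tried. Solving for the student load that gives 0.82 at seven waves, and holding the total fixed, gives:

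| Two-sided alpha | Students per school-period | Total | 4 waves | 7 waves | 10 waves |
|---|---|---|---|---|---|
| 0.05 | 1.8 | about 950 | 0.76 | 0.82 (solved) | 0.84 |
| 0.025 | 2.2 | about 1,160 | 0.75 | 0.82 (solved) | 0.84 |

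The article states 0.75, 0.82 and 0.84, so its figures fit a calculation on Cohort 1 alone. Excluding Cohort 2 therefore takes nothing away from the stated 0.82.

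**What including Cohort 2 could add.** Let c be the information in a Cohort 2 school relative to a Cohort 1 school. The documents do not give c or the number of waves in Cohort 2, so 0.5 to 1 is assumed. Information grows by the factor 1 + c × 33/69, and

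Power = Φ(k × √(1 + c × 33/69) − z), with k = z + 0.915, where Φ(0.915) = 0.82.

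| Two-sided alpha | z | k | c | √ factor | Power |
|---|---|---|---|---|---|
| 0.05 | 1.960 | 2.875 | 0.5 | 1.113 | Φ(1.241) = 0.89 |
| 0.05 | 1.960 | 2.875 | 1 | 1.216 | Φ(1.536) = 0.94 |
| 0.025 | 2.241 | 3.157 | 0.5 | 1.113 | Φ(1.273) = 0.90 |
| 0.025 | 2.241 | 3.157 | 1 | 1.216 | Φ(1.597) = 0.94 |

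In terms of precision, the standard error would be 1/1.113 = 0.90 to 1/1.216 = 0.82 of its Cohort 1 value. The mixed model above, with Cohort 2 spread over all seven waves, gives about 0.83 for 69 schools and 0.94–0.95 for 102. The latter is an upper guide, because Section 2.10.11 expects later schools to have fewer waves.

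**The reason given for exclusion.** Fewer waves means fewer distinct crossover times, and so less information per school. It does not bias a comparison made within Cohort 2's own randomised schedule and conditional on calendar time. The reason supports giving Cohort 2 less weight, which a model with cohort and time terms does by itself. It does not require leaving the cohort out.

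**The case against.** The strongest reply is that the trial does not need Cohort 2. The only power calculation is on Cohort 1, so the literal rule leaves the analysis that was powered. About 90 schools may describe the trial as a whole rather than the primary analysis set. A prespecified exclusion with a stated reason is a choice and not an error, and the schools left out still appear in a secondary analysis. It can also be said that Section 2.10.11 was meant only for schools beyond both cohorts, since it speaks of late enrolment as hypothetical while Section 2.2 reports Cohort 2 as already randomised.

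Much of this stands. The stated power is unaffected. The fewer-waves reason may well describe Cohort 2. The planned secondary analysis means that its data are not simply discarded. The last reading is possible, but nothing in the article states it, and that gap is itself the defect.

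Three stronger readings are tempting and should not be drawn:

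- A reader might infer that the exclusion leaves the trial underpowered. It does not, because 0.82 was computed for 67 Cohort 1 schools.
- A reader might infer that the analysis set could be picked after seeing results. Section 2.6 has exclusion criteria finalised while the analyst works on shuffled data, which largely guards against this.
- A reader might infer from the 122 participants in Section 3 that recruitment is slow and Cohort 2 is needed as a rescue. The article gives neither a submission date nor a participant target, so no rate or shortfall can be derived.

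The difference between 67 and 69 may only reflect counts taken at different times and carries little weight alone.

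**Conclusion.** The point holds as an unresolved conflict over the primary analysis set. As written, Section 2.10.11 takes 33 of 102 schools (32%) out of the primary analysis, while Section 2.1 describes a design that cannot be filled without them. The most likely explanation is that the rule was not updated after Cohort 2 was added.

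The consequence is forgone precision and not a fault in the stated power: illustratively, power of about 0.89–0.94 in place of 0.82. That range rests on an assumed 50–100% relative information per Cohort 2 school and on the plan's own planning inputs. The case for inclusion rests on Cohort 2 having been properly randomised within itself, which Sections 2.2 and 2.5 both report. The matter should be settled, but it does not threaten the validity of the trial.

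**What to change.** Before the analyst blind is broken:

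1. State that the primary analysis includes all schools randomised in Cohorts 1 and 2. Add a cohort term and cohort-specific calendar-time terms, and take each school's phase from its own cohort's randomised schedule.
2. Limit the exclusion in Section 2.10.11 to schools that join outside these two randomisations.
3. Report Cohort 1 alone as a sensitivity analysis, since this is the set on which power was based.
4. Reconcile the school counts (about 90, 69 + 33, and 67), and say which of them describes the trial, the primary analysis and the power calculation.

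The cost is revised wording and a few extra model terms, with no new data. The price in the analysis is a less balanced distribution over waves in Cohort 2, which the cohort-specific terms and the Cohort 1 sensitivity analysis would make visible.

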#### 2.10.12. Power

We determined power using the R package “swCRTdesign” (50) which was explicitly designed to estimate power for stepped wedge designs. We were able to power the study using student enrollment data and publicly available data on 2018–2019 drug infraction rates (51) for the 67 schools who agreed to participate as part of Cohort 1. There were 16 schools without infraction rate data. For simplicity, this missing data was imputed by examining 522 schools with complete data, identifying schools that matched in type (e.g., middle school, high school, etc.) and had the closest number of students. Infraction rates from this subset of schools of the same type and equivalent student size were then substituted for the missing values.

The number of participants per cluster will not depend on the schools assigned to the cluster, but rather the number of students in the schools who will have a substance use infraction. We cannot know the exact number in advance, but we can simulate the predicted number of participants via a binomial distribution using student enrollment for the upcoming 2 years and the infraction percentages from 2018 to 2019. Following the proposed stratified randomization scheme we will use in the actual study, schools were assigned to each cluster at the district-level, stratified by whether a district had any middle schools (yes/no) and school size (using a median split of 1,460 for districts with middle schools and 829 for those without). This approach for generating sample sizes was repeated 100 times to integrate over uncertainty and the final estimate of power was obtained by averaging over the repetitions. As noted earlier, to determine the number of waves to use, we examined power assuming four waves, seven waves, and 10 waves.

Additional parameters required for power estimation were the means in the unexposed and exposed study phases and the pooled standard deviation. For simplicity, means were based on the ratio of the proportion of days spent using a drug at the follow-up time point divided by the proportion of days spent using a drug at the baseline visit. This format allowed easy specification of a clinically meaningful effect, comparing an unexposed ratio of 1 (no change) to an exposed ratio of 0.8 (a 20% reduction in use). To estimate the pooled standard deviation for the ratio, we used data collected in a previous study (NCT: 03276221) from 63 high school students, examining (1) the number of days spent using cannabis over a 30-day interval before a baseline visit, and (2) the number of days spent using cannabis before a 7-week visit over an average monitoring period of 22 days (SD of 10 days). The standard deviation for the ratio of the proportion of days spent before the 7-week visit over the proportion of days spent before the baseline visit was 0.79. Finally, values for the intra-class correlation (ICC) and the cluster auto-correlation (CAC) were required. Based on a large meta-analysis (52), we fixed the ICC and CAC to 0.02 and 0.22, respectively. Power was estimated as 0.75 (SD = 0.03) for 4 waves, 0.82 for 7 waves (SD = 0.03), and 0.84 for 10 waves (SD = 0.03).

